### Randomization

Three Chinese clinicians will diagnose and treat every eligible patient individually. Every Chinese clinician will provide CM patterns and the prescription according to every patient’s disease condition. There will therefore be three prescriptions from three Chinese clinicians for every patient at every visit. At the first visit, patient will equally be randomized to one of the following four groups: medical group A, medical group B, medical group C or placebo group. Patients in the CM groups will be given one of three Chinese clinicians’ prescriptions. Patients in the placebo group will be given the placebo simulating the core drug patterns in the previous study. In the whole study, the randomization of group assignment only occurs at the first visit, and the randomization results will be applied to the following visits. In other words, although the patients have to be diagnosed by every clinician for every visit, they always receive the drug prescribed by the clinician who is distributed to them by randomization at the first visit or they receive placebo. Furthermore, in order to avoid the potential bias, every patient’s order to visit three clinicians is randomized at every visit, meaning that the visiting order in which one patient visits the clinicians may be different every time. It is worth mentioning that a web central randomization system is employed to guarantee the quality.

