### Analysis strategy

The analysis will be per intent to treat. The mean and standard deviation shall be applied to the continuous variables, and percentages to the categorical variables. For comparison of two independent samples, the *t* test and analysis of variance will be applied for continuous variables and the chi-square test for categorical variables. In addition, nonparametric tests will also be applied for analysis. The efficacy for patients taking any pharmacologic medicine will be assessed using the method of last observation carried forward.

As mentioned above, the exploration analysis on core drug patterns will only be based on the effective patients in order to guarantee the efficacy of the explored core prescription. The patients’ syndrome and signs, CM patterns and the treatment effect shall be considered during the analysis. The core drug pattern can be concluded from the combination of high correlation and frequency. The core drug patterns must confirm to the CM theory and be accepted by the prestigious Chinese clinicians. The multi-dimension association rule and scale-free networks method will be applied to mine the core drug patterns and drug utilization rule of three Chinese clinicians [15,20-22]. In CM, the disease syndromes and signs, disease pattern and treatment are a dynamic procedure. The disease pattern varies with syndromes and signs. As a result, the treatment varies with the pattern of disease. So we not only explore the core drug patterns of different prestigious Chinese clinicians, but also mine the core drug patterns corresponding to different syndrome combinations and disease patterns.

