## Discussion

The discovery of a new effective prescription in clinical practice is key to the development of new CM. The experiences of prestigious Chinese clinicians are the main source of effective CM. However, the discovery of effective core drug patterns mainly depends on the accumulation of clinicians’ experiences and is always a long process. This study proposes one method used to develop new effective core drug patterns based on the prestigious clinicians’ treatment data. Randomization, placebo control and blinding designs are employed in the study, where three prestigious Chinese clinicians are treated as subjects. To minimize the bias and factitious influence, a web central randomization system and a clinical research data-capture computer system are adopted to assign the group and collect the data, respectively. In the study, we can obtain one or several effective core drug patterns. Unlike previous retrospective studies [15,16], this perspective study has strictly tested the efficacy of Chinese herbal medicine through comparison between a treatment group and a placebo group. Because the exploratory analysis of core drug patterns is based on the effective patients, the results should be more accurate and useful. In a word, the analysis can accelerate and improve the development of new Chinese herbal medicine for discovery of new effective core drug patterns through exploring the treatment data of prestigious CM clinicians.

To guarantee the quality of the study and accuracy of core herb patterns obtained, patients who met the diagnosis of primary insomnia were recruited. In addition, those patients with hypertension, diabetes, stroke and coronary heart diseases are excluded because these patients may demonstrate mixed symptoms or syndromes in the diagnosis that affect the accuracy of prescriptions by clinicians. Patients older than 65 are easily complicated with the diseases mentioned above and then excluded from the study.

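### Core drug patterns are chosen by frequency and correlation in effective patients, which cannot show that the patterns themselves work

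*Protocol article*

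**What the plan says.** The only objective in the Protocol article (Objectives) is to screen effective core drug patterns. Four statements fix how this is done.

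- **Population and rationale** (Analysis strategy): "core drug patterns will only be based on the effective patients in order to guarantee the efficacy". The guarantee is attached to the prescription that the mining yields.
- **Criterion** (Analysis strategy): "The core drug pattern can be concluded from the combination of high correlation and frequency". The tools are association rules and scale-free networks.
- **Final filter** (Analysis strategy): "The core drug patterns must confirm to the CM theory and be accepted by the prestigious Chinese clinicians".
- **Justification** (Discussion): "Because the exploratory analysis of core drug patterns is based on the effective patients, the results should be more accurate and useful".

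The same section adds that syndromes and signs, "CM patterns and the treatment effect shall be considered during the analysis", without saying how.

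The Sample size section sets the arm-level gate: a difference from placebo of more than 0.5 hours in TST change at 4 weeks, with P below 0.05. Once it is met, placebo and any non-effective group are dropped. Mining continues in the effective group and is repeated after each further 30 enrolments until the patterns stay constant. That section speaks of both an effective group and effective patients, and the article gives no patient-level definition.

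On the data available, the Randomization section states: "There will therefore be three prescriptions from three Chinese clinicians for every patient at every visit". Table 1 lists every herb and dose as recorded at weeks 1 to 4.

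**The concern.** None of the stated criteria compares outcomes with and without a pattern. Frequency describes how often a herb is prescribed, and correlation between herbs describes how often they are prescribed together. Acceptance by the clinicians who wrote the prescriptions adds no outcome information. Repeating the mining until the result is constant does not help either, because stable prescribing habits give a constant result whether or not the herbs work.

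The arm-level test can show that one clinician's prescribing as a whole beats placebo. It does not show which part of that prescribing is responsible, yet the efficacy guarantee is attached to the extracted prescription. At stake is the choice of the candidate taken into later development: a common inert herb could be carried forward and a less common active one left behind.

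**Working it through.** The article gives no SD for TST change, placebo response or herb frequencies, and has no figure of its own to reproduce on this point. The values below are assumptions, apart from the 0.5 hour threshold, the four equal arms and the maximum of 300 (75 per arm).

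**1. Frequency among responders.** For a herb in a fraction f of prescriptions, with response p1 when it is given and p0 when it is not, its frequency among responders is f·p1 / (f·p1 + (1−f)·p0).

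- Inert herb, unrelated to active herbs, f = 0.80: p1 = p0, so the frequency is 80%.
- Active herb, f = 0.20, p1 = 0.60, p0 = 0.40: 0.12 / (0.12 + 0.32) = 27%.

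Over a wider range (f of 0.20 to 0.30, added effect 0.5 to 1.0 h, SD 1.0 to 1.5 h, non-specific gain 0.25 to 0.5 h) the active herb reaches 24% to 45%, still far below 80%. In simulations of 4,000 runs with 75 per arm, SD 1.0 or 1.25 h and added effects of 1.0 or 1.5 h, the inert herb ranked above the active one in over 99% of runs when the active herb was in 30% of prescriptions. With the active herb in 50% (SD 1.25 h, added effect 1.0 h), it did so in 95%.

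**2. The other reading.** If effective patients means the whole effective group, nobody is selected on outcome. The herbs then appear at their prescribing frequencies, 80% and 20%, and the ranking is no better.

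**3. What a non-responder comparison adds.** Among non-responders the active herb's frequency is 0.2·0.4 / (0.2·0.4 + 0.8·0.6) = 0.08 / 0.56 = 14%. The contrast is 27% against 14% for the active herb and 80% against 80% for the inert one. Frequency among responders alone does not show this.

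**4. Passing a 0.5 h threshold on placebo.** This applies only if effective means an individual TST gain above 0.5 h. With a normal model the pass rate is 1 − Φ((0.5 − mean)/SD), and the CM mean is the placebo mean plus 0.5 h.

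| Placebo mean gain (h) | SD (h) | Placebo pass rate | CM pass rate | Ratio |
|---|---|---|---|---|
| 0.25 | 1.0 | 0.40 | 0.60 | 0.67 |
| 0.25 | 1.25 | 0.42 | 0.58 | 0.73 |
| 0.5 | 1.0 | 0.50 | 0.69 | 0.72 |
| 0.5 | 1.25 | 0.50 | 0.66 | 0.76 |

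The placebo pass rate is 40% to 50%, which is 67% to 76% of the CM pass rate.

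**5. What a randomised pattern-level contrast can deliver.** Clinicians are blinded (Design), and visit-1 prescriptions exist for all arms before any randomised treatment is taken. A clinician's arm can therefore be compared with placebo among patients for whom that clinician wrote a given pattern. With 75 per arm, SD 1.25 h, an active herb in 30% of prescriptions adding 1.0 h and an inert herb in 80%, simulation gave 1.00 h (SE 0.38) for the active herb's stratum and 0.30 h (SE 0.24) for the inert herb's. The 0.30 h comes from co-prescribed active herb. Two-sided 5% power for a 0.5 h effect, over SD 1.5 to 1.0 h, is 20% to 39% at 30% herb frequency and 45% to 78% at 80%. At the first interim look (80/4 = 20 per arm), a herb in 30% of prescriptions leaves about 6 against 6, so the SE is 1.25·√(2/6) = 0.72 h.

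**The case against.** The strongest defence is that this is a screening step. The Discussion calls the study exploratory and promises a further randomised trial of the core prescription. Efficacy is tested at arm level before mining focuses on the effective group. The treatment effect is to be considered, and details of the mining may sit in cited methods or a fuller protocol. The illustrations also use single herbs, whereas the plan mines combinations.

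Much of this stands, and it lowers the severity. It does not rescue the stated rule. Under the responder reading, non-effective patients have been removed, so considering the treatment effect cannot supply a contrast with them. Under the group reading a contrast would be possible, but the stated criterion does not use one. The arithmetic in step 1 applies equally to a combination treated as present or absent. A later trial does not support a guarantee made now, and it would inherit whichever candidate this step selects.

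Three stronger readings are tempting, and the documents do not support them.

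- *The randomised comparison is thrown away.* It is kept as the arm-level gate. Only at pattern level is it unused.
- *67% to 76% of CM responders would have improved on placebo.* That figure is a ratio of two pass rates. It equals such a share only if treatment never turns a would-be improver into a non-improver. If the two potential outcomes were independent, the share would be the placebo rate, 40% to 50%. The trial cannot identify it.
- *The study repeats the limitation its authors admit in their earlier work.* The Background names data quality and unvalidated efficacy, not prescribing habit. Prospective data capture and the placebo gate address both.

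**Conclusion.** The point holds at pattern level. As written, the mining identifies what is commonly prescribed in an effective arm or among improvers. It cannot guarantee the efficacy of the extracted prescription, and the restriction to effective patients does not make the result more accurate. This follows from the stated criteria under either meaning of effective patients. The size (80% against 27% in the main illustration) rests on assumed frequencies and response rates and on the inert herb being unrelated to active ones; the inert herb stayed well ahead across the ranges tried. Because the work is labelled exploratory and a confirmatory trial is promised, this should be fixed but does not invalidate the trial.

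**What to change.** 1. State one definition of effective patients and use it in both Sample size and Analysis strategy.
2. Mine all patients in the effective clinician's group. For each candidate pattern, report its frequency in responders and non-responders. Also report, with an interval, the randomised TST contrast between that clinician's arm and the placebo patients for whom the same clinician wrote the pattern at visit 1. Use patients randomised before any dropping of placebo.
3. Use these contrasts alongside frequency to prioritise candidates, and record the data-derived list before the clinicians review it.
4. Replace the guarantee in Analysis strategy and the accuracy claim in Discussion with a statement that the patterns are candidates for the later trial.

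**Cost.** Items 1 and 4 are wording. Items 2 and 3 need programming but no new data items. The contrasts will be imprecise, especially after an early stop, because later recruits then have no placebo comparator. They reflect the whole prescription rather than one herb, since herbs are co-prescribed. Prescriptions can be adjusted later, so a visit-1 pattern does not describe all four weeks of treatment. Ranking many patterns also brings its own selection error, so the number examined should be reported.

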**Methods/design:**

A triple-blind, randomized, placebo-controlled, parallel-group clinical trial will be performed. Three clinicians will diagnose and treat every eligible patient individually and independently, producing three prescriptions from three clinicians for every patient. Patients will equally be randomized to one of four groups – medical group A, medical group B, medical group C, or placebo group – and observed for efficacy of treatment. The sample will include primary insomnia patients meeting DSM IV-TR criteria, Spiegel scale score >18, and age 18 to 65 years. A sequential design is employed. Interim analysis will be conducted when between 80 and 160 patients complete the study. The interim study could be stopped and treated as final if a statistically significant difference between treatment and placebo groups can be obtained and core effective drug patterns can be determined. Otherwise, the study continues until the maximum sample size reaches 300. Treatment of the CM group is one of three Chinese clinicians’ prescriptions, who provide independently prescriptions based on their own CM theory and the patient’s disease condition. Assessment will be by sleep diary and Pittsburgh sleep quality index, and CM symptoms and signs will be measured. Primary outcome is total sleep time. Assessment will be carried out at the washout period, weeks 1, 2, 3, and 4 and 4th week after the end of treatment. Effectiveness analysis will be per intent to treat. A multi-dimension association rule and scale-free networks method will be used to explore the effective core drug patterns.

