### Statistical methods

#### Sample size

The study is supposed to explore the daily clinical practice of three prestigious Chinese clinicians in primary insomnia treatment and to figure out the effective drug patterns prescribed by them. However, it is very difficult to estimate the sample size because of lack of a previous relevant study. To obtain expected results with a minimal sample size, a sequential design will be employed. The interim analysis will be conducted when the total number of patients having completed the study reaches 80 and 160 separately, for which we set up the early stopping criteria. The interim study can be treated as final if the difference in TST changes from baseline at 4 weeks between the CM and placebo groups is >0.5 hours and has statistical significance with *P* <0.05. When the early stopping criteria are met, the placebo group and the non-effective group will be dropped. The subsequent study will only focus on the effective group to explore the core drug patterns. If the number of effective patients is not sufficient to determine the core drug patterns, the recruitment procedure has to continue. The core drug pattern analysis shall be carried out every time the increment of new enrollment reaches 30 until the core drug patterns are obtained and kept constant.

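### The set mined for effective core drug patterns is not consistently tied to the randomised comparison, and nothing limits it to arms that beat placebo if the trial runs to 300

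*Protocol article*

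**What the plan says.** Four parts of the Protocol article bear on which patients are mined.

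- **Sample size.** The early stopping criterion compares the 4-week change in TST between the CM and placebo groups: more than 0.5 h, with P < 0.05. It then says: "When the early stopping criteria are met, the placebo group and the non-effective group will be dropped". The next sentence reads: "The subsequent study will only focus on the effective group to explore the core drug patterns". The one after that changes the unit from group to patient: "If the number of effective patients is not sufficient to determine the core drug patterns, the recruitment procedure has to continue".
- **Analysis strategy.** The restriction is put at patient level, with a stated purpose: "the exploration analysis on core drug patterns will only be based on the effective patients in order to guarantee the efficacy of the explored core" (that is, the formula that mining yields). Further on, the association-rule and network methods "will be applied to mine the core drug patterns and drug utilization rule of three Chinese clinicians". The section closes by repeating that patterns of the different clinicians will be explored.
- **Abstract, Methods/design.** If the interim conditions are not met: "Otherwise, the study continues until the maximum sample size reaches 300".
- **Discussion.** The expected product is stated as: "In the study, we can obtain one or several effective core drug patterns". The same paragraph credits the placebo comparison with testing efficacy, and credits the restriction to effective patients with making the results more accurate.

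The article does not define an effective patient. Its one efficacy criterion, in the Total Sleep Time (TST) section, requires an improvement above 0.5 h that is also statistically significant.

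**The concern.** The objective is to screen effective core drug patterns, and the randomised comparison with placebo is the only evidence in this design that a clinician's prescriptions work. A patient who sleeps longer in an arm that does no better than placebo may show placebo response or natural course. That patient's herbs have not been shown to do anything. Selecting improvers therefore cannot guarantee efficacy, which is the purpose the Analysis strategy gives for it. Only a condition on the arm can support the word effective.

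Two things are at stake. First, patterns of a clinician whose arm failed against placebo could be reported as effective and taken into the next trial. Second, the number of effective patients decides whether recruitment continues, so an unclear definition leaves a recruitment rule unclear too.

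**Working it through.** **Step 1: set the rules side by side.**

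| Question | Sample size section | Analysis strategy section |
|---|---|---|
| Unit of selection | Group, then patient in the following sentence | Patient |
| Must the clinician's arm beat placebo? | Yes, once the early stopping criteria are met | Not stated, except through a back-reference |
| Clinicians covered | The effective group | Three, with no restriction |
| Applies if the criteria are never met and the trial reaches 300? | Not stated | Yes, no condition attached |
| Effective patient defined? | No | No |

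**Step 2: can the TST criterion fill the gap?** It combines a size (more than 0.5 h) with statistical significance. Significance belongs to a group comparison, so the criterion cannot classify a single patient. It says when efficacy is confirmed. It does not say whose prescriptions are mined.

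**Step 3: is the early stopping gate itself per arm?** The contrast is written as CM against placebo. Dropping a non-effective group suggests that arms are judged separately, but no per-arm rule is given. If the CM arms were pooled, an inert arm could pass. With assumed true gains over placebo of 1.0, 1.0 and 0 h and equal arms, the pooled gain is (1.0 + 1.0 + 0)/3 = 0.667 h, above 0.5 h.

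**Step 4: an illustration of size.** The article gives no SD, no expected placebo change and no power, so there is no stated figure to reproduce. Equal allocation to four groups gives 80/4 = 20, 160/4 = 40 and 300/4 = 75 per arm.

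Assumptions, none of them from the article:
- effective patient = individual TST gain above 0.5 h
- normally distributed change
- SD 1.0 to 2.0 h
- mean change m of 0 to 0.75 h in an arm no better than placebo

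Formula: P(gain > 0.5 h) = 1 − Φ((0.5 − m)/SD).

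| m (h) | SD 1.0 | SD 1.5 | SD 2.0 | Expected number of 75 |
|---|---|---|---|---|
| 0 | 0.309 | 0.369 | 0.401 | 23.1 to 30.1 |
| 0.25 | 0.401 | 0.434 | 0.450 | 30.1 to 33.8 |
| 0.50 | 0.500 | 0.500 | 0.500 | 37.5 |
| 0.75 | 0.599 | 0.566 | 0.550 | 41.2 to 44.9 |

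The range is 0.309 to 0.599, or about 23 to 45 patients in one such arm at 300. If no clinician beat placebo, the three CM arms (3 × 75 = 225) would still yield 225 × 0.309 = 69.5 to 225 × 0.599 = 134.8, about 70 to 135 patients who could be mined as effective.

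**The case against.** The strongest reply is that the sections can be read together. The restriction in the Analysis strategy opens with a back-reference: "As mentioned above, the exploration analysis on core drug patterns will only be based on the effective patients". The text it points to is the Sample size section, where effective patients appear one sentence after the effective group. On that reading they are patients within winning arms, and naming three clinicians only describes the general scope of the methods. This stands as a fair reading. A reader might infer that the article sets two flatly conflicting populations, or that it orders mining of the effective patients of all three clinicians. It does not. That second reading joins two separate sentences. The back-reference does not settle the matter either, because it leads to a rule written only for the case where the early stopping criteria are met.

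A second reply is that the TST section already withholds confirmed efficacy from an arm without a significant gain, and that the Discussion says only what may be obtained. So the article does not commit anyone to calling a failed arm's patterns effective. That is correct. But nothing prevents it, because the TST criterion does not choose the mining set.

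Third, the Discussion plans a further randomised trial of the core prescription. This softens the harm, but that trial would test whichever pattern emerged, so a pattern drawn from an inert arm would waste it.

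Fourth, a definition of effective patient could sit in a fuller document. Its absence alone would be no finding. The finding is that the article does state the mining population, words it differently in two places, and claims that the patient-level choice guarantees efficacy.

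**Conclusion.** The point holds as an ambiguity with a real consequence. The link between the mining set and the randomised comparison is explicit only after early stopping, is not clearly per arm even there, and is not stated for a trial that reaches 300 without meeting the criteria. Improvers from an arm no better than placebo could then supply patterns labelled effective.

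The 30% to 60% figure rests wholly on an assumed definition of effective patient and on assumed means and SDs. It shows that the number could be substantial and does not estimate what will happen. It would also be tempting to set it against a figure of zero under the Sample size rule. That comparison is not secure, because a pooled contrast could let an inert arm through there as well.

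The wording should be corrected, since the claim of efficacy for the trial's main product depends on it.

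**What to change.** Use one rule in the Sample size, Analysis strategy and Discussion sections:

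1. Mining that supports an effective core drug pattern uses only clinician arms that individually met the existing criterion against placebo (TST gain above 0.5 h and statistically significant). This applies at the looks at 80 and 160 and at the final analysis at 300.
2. Effective patient is defined, and effective patients are selected and counted only within those arms, including for the decision to continue recruitment.
3. Patterns of a clinician whose arm did not meet the criterion may be reported as prescribing patterns, without the word effective.
4. If no arm meets the criterion, the report states that no effective core pattern was found.

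The statement that selecting effective patients guarantees efficacy should be removed, or made to depend on the arm's result. The change takes a few sentences and needs no new data or patients. The cost is that each per-arm comparison at 300 rests on 75 against 75 patients, where a pooled one would have 225 against 75. Fewer clinicians' patterns, and possibly none, may then be called effective.
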